#### Strategies to improve adherence to interventions {11c}

In order to improve adherence to interventions, researchers will continuously request feedback from the participants throughout the sessions to check for possible discomfort and adjust the exercises execution if it is needed. Moreover, every session will be supervised by at least two researchers with experience in exercise rehabilitation, to ensure the patients are executing the exercises properly.

#### Relevant concomitant care permitted or prohibited during the trial {11d}

Participants will be allowed to keep their pharmacological treatment during the entire study. However, participants will be excluded in case of any dose modification during the trial. In addition, participants may continue to attend physiotherapy interventions and any other non-pharmacological interventions if it is a regular practice started at least 6 months before the study. In this case, participants will be requested to maintain this activity during the entire study; otherwise, they will be excluded.

However, they will be excluded in case of suspension of any intervention or start of a new regular intervention. For the outcome assessments performed at baseline and after the intervention program, participants will be instructed not to drink alcohol and/or stimulants (coffee, teas, and energy drinks), avoiding heavy meals, having a light meal at least 2 h before the test and not doing strenuous exercise 48 h before the evaluations.

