Besides motor abnormalities, patients with PD present non-motor symptoms such as dysautonomia [14] and sleep disturbances [15]. Thus, physical exercise has been highly recommended as non-pharmacological intervention since it has shown to attenuate motor dysfunction, improve cognitive function, effectiveness of medications, and sleep patterns, as well as prevent depression and cardiovascular complications [16]. In this sense, Amara et al. mention that regular practice of physical exercise has positive effects on the effectiveness of sleep in the long term for patients with PD [17]. Furthermore, according to Fan et al. [18], physical exercise, especially those performed at moderate to vigorous intensities, has a positive impact on PD through multiple mechanisms, including reduction of α-synuclein protein accumulation, decrease in inflammation and oxidative stress, improvement in brain-derived neurotrophic factor (BDNF) activity, nerve regeneration, and mitochondrial function. Furthermore, some authors have shown that endurance exercise is safe and well-tolerated for people with PD from a cardiovascular point of view, which supports their recommendation for this population [19].

Although physical exercise has shown to be effective, some authors have proposed other non-pharmacological strategies as complementary therapy. In this sense, Barbic et al. [20] proposed an innovative approach aiming at improving walking parameters in PD. The authors evaluated the effect of a single session of peripheral mechanical stimulation therapy. After the stimulus, the authors observed significant changes in motor parameters such as improvement in gait length and gait speed. Concomitant to the motor improvement, surprisingly, there was an improvement in some cardiovascular parameters, such as decreased resting blood pressure and improved cardiovascular autonomic control in response to orthostatic stimulation. In addition, Zamunér et al. [21] studied the effects of five sessions of automated mechanical peripheral stimulation (AMPS) on cardiovascular parameters in patients with PD. The authors reported that after the AMPS therapy, patients with PD presented a decrease in cardiovascular sympathetic control and an improvement in arterial baroreflex sensitivity.

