### Eligibility criteria {10}

#### Inclusion criteria

Volunteers must present a clinical diagnosis of PD, made by a board-certified neurologist, according to the UK Brain Bank criteria [24] aged 50 years or over and be classified as 1 to 3 at the Hoehn and Yahr scale. Drug treatment of volunteers should remain unchanged for at least 30 days prior their inclusion in the study.

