#### Exclusion criteria

Volunteers who show signs of cognitive impairment, based on the results of the Mini-Mental State Examination adjusted for the educational level of the Chilean and Brazilian population [25], who present cardiorespiratory, neuromuscular, and musculoskeletal diseases will be excluded. Volunteers who have peripheral sensory neuropathy, diabetes, or any other condition or disease known to promote autonomic dysfunction will be excluded based on symptoms, physical condition, and routine laboratory tests.

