#### Intervention description {11a}

##### Automated mechanical peripheral stimulation

AMPS therapy will be applied through a therapeutic device (Gondola, Ecker Technologies, Lugano, Switzerland), which will be fitted to each patient’s feet. The device consists of a foot stand for each foot with two electric motors that activate two 2-mm-diameter metal bars. The mechanical pressure stimulus occurs when the motors are activated. Before application, the device is adjusted so that the stimulus is applied to two specific areas for each foot, at the base of the first metatarsal joint and at the head of the hallux of the right and left feet. The intensity of the pressure is adjusted to reach the participant’s pain threshold (which normally occurs around 0. 3–0. 9 N mm^2^), defined as the moment when the participant reports that they began to feel pain (the moment of transition between the strong pressure and the painful pressure and the first time the visual analog scale (VAS) is greater than 0) or at the moment when the monosynaptic reflex appears in the anterior tibial muscle. After these preparatory procedures, treatment begins. The therapy will be carried out in 4 cycles. A cycle is completed when the four target areas are stimulated, which requires 24 s (6 s per area) so the complete therapy lasts 96 s [26].

The SHAM intervention will replicate the same procedure described for active AMPS. However, a rubber adapter will be positioned at the tip of the metal bars to increase the contact surface area and the pressure will be set to the sensorial threshold (i.e. when the patient report that they feel a touch at the point). AMPS sessions will be performed 24 h before all the exercise sessions [27].

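### Earlier or current AMPS use is not restricted at entry, and the concomitant-care rule, read literally, makes a long-term AMPS user continue it even in the sham arm

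*Protocol article*

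**What the plan says.** All references are to the protocol article.

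- **Inclusion criteria.** The only treatment that must be stable at entry is medication: "Drug treatment of volunteers should remain unchanged for at least 30 days prior their inclusion in the study".
- **Exclusion criteria.** These cover cognitive impairment, several disease groups and causes of autonomic dysfunction ("Volunteers who have peripheral sensory neuropathy, diabetes, or any other condition or disease known to promote autonomic dysfunction will be excluded"). AMPS is not mentioned.
- **Concomitant care {11d}.** Participants may continue physiotherapy and "any other non-pharmacological interventions if it is a regular practice started at least 6 months before the study". For those who do, "participants will be requested to maintain this activity during the entire study; otherwise, they will be excluded". AMPS is not excepted.
- **Background {6a}.** AMPS is introduced directly after the statement that "some authors have proposed other non-pharmacological strategies as complementary therapy". The Abstract and Discussion also call it a complementary therapy.
- **Intervention description {11a}.** For active AMPS, "The intensity of the pressure is adjusted to reach the participant’s pain threshold". The sham stimulus is blunted by a rubber tip that widens the contact area, and its intensity differs too: "the pressure will be set to the sensorial threshold".
- **Choice of comparators {6b} and blinding {17a}.** Both arms receive the same exercise programme and differ in active versus sham stimulation. Participants are meant not to know which they receive.
- **Unblinding {17b}.** A participant who reports knowing their group is excluded from the study.

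**The concern.** The trial asks whether AMPS adds anything to exercise, and the sham arm exists to isolate that. Two gaps work against it.

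First, nothing at entry screens out people who already know the sensation of active AMPS. The sham differs from it in contact area and in intensity (touch against the onset of pain). A person with earlier experience, even a short one, has a direct basis for telling which they are receiving. PDQ-39 is a primary outcome and is self-reported, so expectation can move it. A participant who says they have recognised their arm is then removed after randomisation, possibly at different rates in the two arms.

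Second, the duty to maintain existing non-drug therapies makes no exception for the therapy under test. Applied as written, it would have a sham participant go on receiving AMPS outside the trial and would remove that person for stopping.

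**Working it through.** The protocol gives no figure for AMPS use among potential participants, so the check is mainly of the text.

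**Step 1: does AMPS fall within the permitted class?** {11d} covers any regular non-drug intervention begun at least 6 months earlier. The Background presents AMPS as one of the non-drug complementary strategies. By the protocol's own description it belongs to the class.

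**Step 2: does another section take it out?** The inclusion list requires stability of drugs only. The exclusion list has no item on treatment history. The discontinuation criteria {11b} cover attendance, absence at evaluations and newly started exercise. None restricts AMPS, so the literal rule stands: enter, maintain, or be excluded.

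**Step 3: who is affected?**

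| Exposure | Caught by the maintain rule? | Barred at entry? | Risk |
|---|---|---|---|
| Regular AMPS for 6 months or more | Yes | No | Contamination and recognition of the sham |
| Earlier or short AMPS exposure | No | No | Recognition of the sham |

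The blinding risk covers both rows and the contamination risk only the first.

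**Step 4: what follows from recognition?** {18a} and {12} make PDQ-39 a self-reported primary outcome. {11a} asks participants to guess their arm and rate their confidence at 6 weeks and at the end. That measures unblinding but does not prevent it. {17b} turns reported recognition into exclusion, and because {16c} has the envelope opened only after baseline assessment, that exclusion falls after randomisation.

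**Step 5: can contamination be turned into a percentage?** The planned parametric test {20a} is the group-by-time interaction, a difference in change from baseline. Let E be the change due to exercise and δ the effect of AMPS, and suppose a long-term user is at steady state.

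| Participant | Change if AMPS simply adds δ | Change if AMPS potentiates exercise by δ |
|---|---|---|
| Ordinary, sham | E | E |
| Ordinary, active | E + δ | E + δ |
| Long-term user, sham | E (δ present at both visits) | E + δ |
| Long-term user, active | E (δ already in baseline) | E + δ |

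If the effect is additive, only a user in the active arm reduces the contrast. If AMPS works by potentiation, the route the Background and Discussion describe for exercise performance, only a user in the sham arm does. The fallback Mann-Whitney test could behave differently again if applied to final values. The size therefore depends on a mechanism that the protocol does not settle and on a number of users that it does not give.

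**The case against.** The strongest reply is that the affected population is small. The maintain rule reaches only regular users of 6 months or more. The Discussion calls AMPS relatively new, and the Background says that programmes lasting more than 1 month have not been studied. The protocol offers AMPS after the trial if it proves effective, which suggests that participants are not expected to have it already. This stands, and it is why contamination is the lesser part of the point.

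A second reply is that concomitant care ordinarily means usual care alongside the trial treatment, with physiotherapy as the example, and that a condensed article may leave a detailed screening list to the full protocol. This stands in part. The literal reading is probably unintended. Even so, eligibility and concomitant care are both set out here, and the rule as stated produces the conflict; it is not only a missing detail.

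A third reply is that a pain-level active treatment against a touch-level sham tests blinding for every participant. That is true, but an experienced participant has a comparison that a naive one lacks.

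A reader might infer two stronger points that the documents do not support:

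- **A fixed loss per user.** With 25 per arm, one might say that each AMPS user in either arm removes one twenty-fifth of the effect. Step 5 shows that this does not follow for a change-from-baseline comparison.
- **Likely exposure through recruitment.** One might suppose that recruitment draws on centres where AMPS is in use. The Recruitment section names radio and online advertising, notices, neurological clinics and public family health centres, and does not say that any of them provides AMPS.

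**Conclusion.** The point holds as a conflict between a stated rule and the sham-controlled design. Earlier and current AMPS use is unrestricted, and the concomitant-care rule, taken literally, obliges a long-term user to continue in either arm. The main realistic consequence is weakened blinding of the self-reported PDQ-39, with possible exclusions after randomisation. Contamination by current long-term users is possible but probably rare.

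Neither effect can be sized. The documents give no prevalence of AMPS use, and the direction of any dilution depends on how AMPS acts. The conclusion rests on two assumptions: that AMPS counts as a non-drug intervention, as the protocol describes it, and that prior experience helps a person to tell pain-threshold stimulation from touch. It does not imply that contaminated or unblinded participants will occur in numbers that matter. This is a cheap improvement of minor to moderate weight.

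**What to change.** 1. In the exclusion criteria, add earlier or current treatment with AMPS, including in a pilot or an earlier AMPS study. One screening question is enough to check it.
2. In {11d}, reconcile the duty to maintain existing therapies with the sham control, so that AMPS outside the trial does not fall within it.

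The cost is an amendment through the route described in {25}, one extra question at screening, and the loss of a few volunteers with earlier exposure. No sample size, outcome or analysis changes. The Trial status section shows that recruitment began before the current version, so the same question could be put to those already enrolled and the answers reported by arm.

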#### Provisions for post-trial care {30}

At the end of the study, if AMPS is effective in promoting higher improvement than exercise alone, the same treatment will be offered at no cost to EX-G participants.

#### Outcomes {12}

The results will be evaluated at 2 time points: (1) baseline (before starting the intervention program) and (2) after 12 weeks of intervention (after 48 h to 1 week from the last intervention). The primary outcomes will be (1) quality of life (PDQ-39), (2) heart rate variability (HRV) indices, and (3) VO2peak (cardiopulmonary exercise testing). Secondary outcomes include (1) 24-h blood pressure (3 channel Cardio Map digital equipment), (2) sleep quality (actigraph monitor), (3) VO2 at the anaerobic threshold (cardiopulmonary exercise testing), (4) dynamic balance (Tinetti Scale, TUG), and (5) gait velocity (10-m Walk Test).

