### Objectives {7}

The objectives of this study will be to evaluate the effect of 24 sessions of AMPS combined to a physical exercise program performed twice a week for 12 weeks on aerobic functional capacity, gait parameters, and cardiac autonomic control in patients with PD. As a hypothesis, the exercise program combined with AMPS therapy is expected to be more effective in improving cardiac autonomic control and aerobic functional capacity in PD patients than exercise alone.

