##### Heart rate variability

HRV is defined as the variation that occurs in the time interval between consecutive heartbeats and it has been proposed that its behavior depends on autonomic modulation, as well as its implications on cardiovascular mortality [31]. This time it will be done by continuous recording of RR intervals with 1000 Hz sampling frequency (Polar V800, Finland). R-R intervals will be recorded with a Polar V800 heart rate monitor (Polar, Oi, Finland); a sensor will be placed on the chest at the fifth intercostal space. Prior the beginning of data collection, volunteers will remain at rest for approximately 20 min for baseline heart rate and BP stabilization. Recording will occur under the following conditions: (1) resting in supine position for 15 min and (2) resting in orthostatic posture for 15 min. The volunteers will be instructed to maintain spontaneous breathing throughout the collection period in the supine and orthostatic postures. The participants’ respiratory rate will be recorded throughout the test. Heart rate variability will be analyzed through spectral analysis in an autoregressive model. The spectral components will be obtained at low frequency (LF, 0.04–0.15 Hz) and high frequency (HF, 0.15–0.4 Hz). The LF band is modulated by the sympathetic and parasympathetic autonomic nervous system (with sympathetic predominance), the HF band is associated with cardiac vagal control, and the LF/HF ratio is calculated to assess sympathovagal balance.

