### Statistical methods

#### Statistical methods for primary and secondary outcomes {20a}

The Shapiro-Wilk and Levene’s tests will be applied to check for data normality and the homogeneity of the variance, respectively. To check the interaction between the Groups (EX-G and AMPS-G) and time (baseline and post-intervention) a mixed ANOVA model with Bonferroni adjustment will be applied for the variables that meet the ANOVA assumptions. Otherwise, the data will be analyzed by the Wilcoxon (intragroup) and Mann-Whitney (intergroup) tests with a priori Bonferroni correction. For all tests, the significance level will be set at 5%.

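### Three unranked primary outcomes, one an open set of HRV indices, with no success rule and a Bonferroni adjustment whose family is undefined, so 5% control across the primaries cannot be established

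*Protocol article*

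**What the plan says.** Outcomes {12} lists the primaries: "The primary outcomes will be (1) quality of life (PDQ-39), (2) heart rate variability (HRV) indices, and (3) VO2peak (cardiopulmonary exercise testing"). Nothing there or elsewhere orders them or says whether one, two or all three must show a difference.

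The Heart rate variability section says what the second primary could contain. Recordings are made in two conditions, "1) resting in supine position for 15 min and (2) resting in orthostatic posture for 15 min". On the analysis, "The spectral components will be obtained at low frequency" and at high frequency, and "the LF/HF ratio is calculated to assess sympathovagal balance". No index or posture is singled out.

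Statistical methods {20a} covers primary and secondary outcomes together. On the parametric route, "a mixed ANOVA model with Bonferroni adjustment will be applied for the variables that meet the ANOVA assumptions". Other variables go to Wilcoxon (within group) and Mann-Whitney (between groups) "tests with a priori Bonferroni correction". The paragraph closes: "For all tests, the significance level will be set at 5"%. The set of comparisons and the divisor are given for neither route.

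Sample size {14} uses a 95% confidence level and 80% power, with no division of alpha. Objectives {7} sets out to evaluate the effect "on aerobic functional capacity, gait parameters, and cardiac autonomic control in patients with PD"; quality of life is not in that list.

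**The concern.** With several primary outcomes, the plan has to say what counts as a positive trial and how the 5% is shared. Here both are open. One of the three primaries is itself a group of results from which a favourable index or posture could be picked after the fact. If each result is judged at 5%, a single nominally significant finding among many could be reported as a positive primary result, and the real false-positive risk would be well above 5%.

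Bonferroni is named, so everything turns on what it covers. The lists of aims add to the uncertainty: the primary list includes quality of life, which Objectives {7} omits.

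**Working it through.** **Inputs.** Three named primaries (Outcomes {12}). HRV: 3 quantities × 2 postures = 6 possible results (Heart rate variability section). Alpha 0.05 for all tests ({20a}). Effect size 0.80, 19 per group, 25 enrolled per group (Sample size {14}). The article gives no correlations, so those below are assumptions.

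**Step 1. The plan's own figure.** The only related figure is the 19 per group. Reading 0.80 as a standardised difference between two means, n per group = 2(z_alpha + z_power)²/d², with z_power = 0.842.
- One-sided 5%: 2(1.645 + 0.842)²/0.64 = 19.3 (20 rounded up; 21 with the exact t-test).
- Two-sided 5%: 2(1.960 + 0.842)²/0.64 = 24.5 (25; 26 with the t-test).
- One-sided 0.05/3: 2(2.128 + 0.842)²/0.64 = 27.6 (28).
- Two-sided 0.05/3: 2(2.394 + 0.842)²/0.64 = 32.7 (33; 35 with the t-test).

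The stated 19 is close only to a one-sided test at an undivided 5%; the article does not give sidedness. On neither reading does it fit alpha split over three outcomes. This is a pointer, not proof, because the effect size is for systolic blood pressure, and 24-h blood pressure is a secondary outcome.

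**Step 2. What Bonferroni could cover.** With two groups and two times, the group-by-time interaction has (2 − 1)(2 − 1) = 1 degree of freedom. It amounts to comparing mean change between groups. If the adjustment is a post hoc one on pairwise means, it leaves the interaction p-value as it was. On the other route, the correction could refer to the within-group and between-group tests of one variable. Because the route is chosen variable by variable, a correction across outcomes would need a family spanning both routes, and none is given.

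**Step 3. Error if it does not span the primaries and any one success counts.** For k independent tests, error = 1 − 0.95^k.
- k = 3: 1 − 0.95³ = 14.3%.
- k = 8 (PDQ-39, VO2peak, six HRV): 1 − 0.95⁸ = 33.7%.

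**Step 4. Correlated tests** (multivariate normal simulation, 1,000,000 draws, two-sided 5%).

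| Setting | Assumed correlation | Error |
|---|---|---|
| 3 tests, common correlation | 0.3 / 0.5 / 0.7 | 13.6% / 12.6% / 10.9% |
| 8 tests, only the six HRV tests correlated | 0.3 / 0.5 / 0.7 / 0.9 | 31.6% / 28.4% / 24.6% / 19.5% |
| 8 tests, log LF/HF derived from log LF and log HF | LF–HF 0.3 to 0.8, postures 0 to 0.7 | about 27% to 30% |

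**Step 5. Error if it does span them.** At 0.05/3 per test, with three independent tests, error = 1 − (1 − 0.0167)³ = 4.9%. If instead all three primaries had to succeed, each at 5%, the error would be at most 5%.

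**The case against.** Bonferroni is named on both analysis routes, and a 5% level for all tests is compatible with it, since Bonferroni is one way of holding an overall 5%. If it spans the primaries, there is no inflation. A reader might infer that the plan has no control across outcomes. The article does not say so, and that reading should not be put to the sponsor as fact. What stands is that the family is undefined and that the surrounding text leans against one spanning the primaries.

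A reader might also take 14% to 34% as the trial's actual error rate. It is not. It requires that Bonferroni does not span the primaries, that any one success counts, and that the tests are independent. Independence is untenable at the upper end, because LF/HF is computed from LF and HF and both postures come from the same patients. Nor is 34% a firm ceiling: no PDQ-39 score is chosen, and eight dimensions tested separately would make 15 tests (8 + 6 + 1), or 1 − 0.95¹⁵ = 54% if independent.

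It is likewise too strong to say that quality of life is primary without any hypothesis. The abstract's discussion expects greater gains with AMPS, quality of life among them, and the main Discussion repeats this. The gap is confined to Objectives {7}. That gait is an objective but gait velocity is secondary is not an error in itself, since the objectives are not labelled primary.

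Finally, a statistical analysis plan may fix the divisor, the HRV index and the PDQ-39 score. That is a fair reason not to fault missing detail. But the choice of primary variable and the meaning of success belong in the protocol, and the article addresses outcomes and significance level directly, in a form that leaves both open.

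**Conclusion.** The point holds in conditional form. The primary set is open, no success rule is given, and the Bonferroni family is undefined, so a reader cannot establish 5% control across the primary outcomes. If Bonferroni does not span them and any one significant result counts, the familywise error is up to about 14% for three tests (11% to 14% with correlations of 0.3 to 0.7). For eight tests it is up to about 34% if independent, and about 20% to 32% with HRV correlations of 0.9 down to 0.3. All correlations are assumed, and the count of six HRV tests is the number the measurement section permits, not one that the plan declares. If Bonferroni does span the tested primaries, or if all three must succeed, the error is at most 5%. The plan should be corrected before the analysis.

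**What to change.** Amend the protocol as follows.

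- Name one HRV index in one prespecified posture as the HRV primary. LF/HF is a natural candidate because Sample size {14} already refers to it. Make the other HRV results secondary.
- Use one PDQ-39 summary score as the quality-of-life primary.
- State that 5% is controlled across the three primaries, by Holm or by a fixed sequence with its order written down. A sequence could start with the autonomic and aerobic outcomes, which carry the hypothesis in Objectives {7}, and put quality of life after them.
- Say what any remaining Bonferroni adjustment in {20a} covers.
- Bring Objectives {7} into line with the primary list.

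The article plans no interim analysis and states that assessors and analysts are blinded, so the change can be made without knowledge of results if it is settled before unblinding.

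The cost is wording, plus power per outcome under Holm. For illustration only, take d = 0.80 (a systolic blood pressure effect, not one for a primary outcome), a two-sided t-test and all 25 per group completing. Power is then 79% at 0.05 and 64% at 0.05/3, Holm's strictest step; 80% at 0.05/3 would need 35 per group. A fixed sequence costs the first outcome no power, but later outcomes can be tested only if those before them succeed.
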